### 7.2 Collection, Recording and Reporting of Serious Adverse Events to Ethics Board

Only related SAEs (definitely/ probably/ possibly) will be reported to the Ethics Board of Nanhai Maternity and Children's Hospital of Guangzhou University of Chinese Medicine ( main hospital site) and the Foshan Science and Technology Bureau, Guangdong province. Related means there is a reasonable possibility that the event may have been caused by participation in the clinical trial. The investigator is responsible for informing the Ethics Board after first knowledge that the case qualifies for reporting. Follow-up information will be actively sought and submitted as it becomes available. Related AEs will not be reported to Ethics Board. However, the investigator is responsible to keep record of such AEs cases at the Study Site File.

### 7.3 Safety Monitoring Plan

All data will be entered into a secure password-protected document in the desktop. Access to the data will only be open to the Principal Investigator and Co-Investigators. Hardcopy of the data forms will be stored in a locked cupboard in the department. All adverse events of tPCS in all participants will also be logged and safety of tPCS will be monitored by the Principal Investigator and Co-Investigators.

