## 4.2 Randomization - Allocation Implementation

Subjects who meet the inclusion criteria and have signed consent form will be numbered according to their sequence of the time of visit (from 1 to 340). The administrator will send out the envelope with number corresponding to the number of the subject to the respective hospital of the subject. Upon opening of the envelope, the group allocation is revealed, and the subject is randomized to either the Control (Sham-tPCS) Group or the Intervention (active-tPCS) Group, with 170 subjects in each group.

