## 7 Safety Measurements

### 7.1 Definitions

An adverse event (AE) is any untoward medical occurrence in a clinical investigation subject who is administered a medicinal product or investigational product, and which does not necessarily have a causal relationship with this treatment. An adverse event (AE) can therefore be any unfavorable and unintended sign (including an abnormal laboratory finding), symptom, or disease temporally associated with the use of a medicinal (investigational) product, whether or not related to the medicinal (investigational) product. A serious adverse event (SAE) is any untoward medical occurrence that at any dose:

- results in death
- is life-threatening
- requires inpatient hospitalization or prolongation of existing hospitalization
- results in persistent or significant disability/incapacity, or
- is a congenital anomaly/birth defect

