### **9.2.3 Safety analysis**

Intervention is non-invasive, potential side effects are only limited to influences upon the skin where the electrodes are placed. Participant discomfort will be closely monitored. Urine test will be conducted before and after the intervention to check for any unintended metabolic changes. Adverse event monitoring will be reported in the full study population and described in a table. Chi-Square test will be used for any comparison of the incidence rate of adverse events between the two groups.

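### Adverse events are defined regardless of cause, but the investigator's recording rules depend on cause, and the plan names neither the source of the between-arm comparison nor a blinded judge of relatedness

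*Combined protocol and SAP*

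**What the plan says.** **Definition.** Section 7.1 counts any untoward occurrence, "whether or not related to the medicinal (investigational) product".

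**Recording by investigators.** Section 7.3 says: "All adverse events of tPCS in all participants will also be logged and safety of tPCS will be monitored by the Principal Investigator", together with the co-investigators. Section 7.2 first says that related adverse events do not go to the Ethics Board, then adds: "However, the investigator is responsible to keep record of such AEs cases at the Study Site File". Taken literally, the events so described are the related ones.

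**Reporting outside the site.** Section 7.2: "Only related SAEs (definitely/ probably/ possibly) will be reported to the Ethics Board"; the same rule covers the Foshan Science and Technology Bureau. Appendix 5, A5.1 adds a second route: a monthly report to the monitoring committee (DSMC) with summaries of serious events from each site. No relatedness restriction is stated there.

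**Relatedness.** Section 7.2: "Related means there is a reasonable possibility that the event may have been caused by participation in the clinical trial". It does not say who makes the judgement.

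**Caregiver log.** The note on tPCS under section 4.3 has parents or caregivers in both groups complete an adverse event log after every session.

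**Blinding.** Section 6.4 covers children, caregivers and outcome evaluators. Staff who deliver stimulation and the investigators are not on that list. Active and sham devices stand in different rooms on different floors.

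**Analysis.** Section 9.2.3 reports adverse events in the full study population and says: "Chi-Square test will be used for any comparison of the incidence rate of adverse events between the two groups". It does not name the data source.

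**The concern.** A comparison of adverse events between arms is interpretable only if both arms are counted by the same rule. Sections 7.2 and 7.3 place a causality judgement between the event and the investigator's record. Nothing prevents that judgement from being made with the arm known. Section 4.2 says of the site procedure: "Upon opening of the envelope, the group allocation is revealed", and the separate rooms make the arm visible to whoever works in them. A person who knows that a child receives sham has a reason to call a headache unrelated, and may call the same headache possibly related on active. The opposite can also happen: section 9.2.3 presumes that side effects are confined to the skin, although section 2.4.1 lists headache, so a real non-skin effect on active could be put down to autism.

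The stake is considerable because section 1.2.3 says tPCS has not yet been studied in children with autism. An even-handed safety comparison is therefore one of the trial's main products.

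**Working it through.** The plan gives no figure on this point, so there is none to reproduce. The check is first textual, then an illustration of scale.

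**Which record could feed the section 9.2.3 comparison?**

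| Source | Filtered by cause? | Completed by | Linked to 9.2.3? |
|---|---|---|---|
| Caregiver log (4.3, tPCS note) | No | Blinded caregivers | Not stated |
| Investigator log (7.3) | Worded as events of the stimulation | Person not stated; blinding not stated | Not stated |
| Site file (7.2) | Literally, related events only | Investigator; blinding not stated | Not stated |

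Section 8.2 describes data entry for the ATEC, ABC and CSHQ forms only, and the table of contents lists no adverse event form among the appendices. Section 7.3 says generally that all data are entered in a protected document. That may include the caregiver log, but the log is not named. The comparison can therefore be built from records that follow different rules, and the plan does not choose.

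**Illustration of scale, conditional on the filtered record being used.**

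Inputs from the documents:
- n = 170 per arm (section 4.2).
- Event rates p = 11.5% and 5.8%, the rates of tingling and itching cited in section 1.2.3. They serve only as plausible rates.

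Assumed input:
- k, the share of children with an event whose event is counted in one arm, while the other arm counts all. The documents give no value, so k runs from 100% to 50%.

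Method: the counted rate in the filtered arm is k × p. The test statistic is X² = (p̂₁ − p̂₂)² / [p̄(1 − p̄) × 2/n], significant if X² > 3.8415. The probability of significance is summed exactly over both binomial distributions. For example, at p = 11.5% and k = 50% the expected counts are 170 × 0.115 = 19.6 and 170 × 0.115 × 0.5 = 9.8.

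Equal true rates in both arms:

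| k | p = 5.8%: expected counts | P(significant) | p = 11.5%: expected counts | P(significant) |
|---|---|---|---|---|
| 100% | 9.9 v 9.9 | 4.8% | 19.6 v 19.6 | 5.1% |
| 90% | 9.9 v 8.9 | 5.4% | 19.6 v 17.6 | 6.5% |
| 75% | 9.9 v 7.4 | 9.0% | 19.6 v 14.7 | 14.5% |
| 50% | 9.9 v 4.9 | 25.5% | 19.6 v 9.8 | 48.1% |

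The probabilities are the same whichever arm is filtered.

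Masking a real difference, assuming true rates of 11.5% on active and 5.8% on sham with all sham events counted: the chance of a significant result is 47.3% at k = 100% for active, 16.9% at 75% and 4.8% at 50%. At 50% the counted active rate is 0.5 × 11.5% = 5.75%, level with sham.

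With equal true rates, the ratio of expected counts is simply the ratio of the two attribution rates. Assuming 80% of events called related on active and 20% on sham gives a fourfold ratio by construction. That says nothing about this trial.

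**The case against.** The plan can be read as already all-cause. Section 7.1 defines the term without regard to cause, and section 9.2.3 uses that term, in the full study population, without limiting it to related events. The caregiver log is unfiltered and kept by blinded people in both arms. The sentence in section 7.3 says all events in all participants, sham children included, and may be loose wording for events during the study. Section 7.2 concerns reporting to the Ethics Board, and it does not say that other events go unrecorded.

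Much of this stands, and it rules out three stronger readings that a reader might infer:

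- *That serious events judged unrelated reach no outside body.* Appendix 5, A5.1 sends serious-event summaries to the DSMC with no stated relatedness filter. The related-only rule is confined to the Ethics Board and the Bureau.
- *That the chi-square test will use filtered counts.* This is possible but not established.
- *That whoever decides relatedness is unblinded.* Section 4.2 does not say who opens the envelope, and section 6.4 merely leaves investigators off the list of blinded people. What can be said is that the person who decides, and the blinding of that person, are unspecified.

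The objection does not remove the gap. The only recording duties placed on investigators, in 7.2 and 7.3, are narrower than the definition in 7.1, and no sentence carries the caregiver log into the safety table. The DSMC route covers serious events only, and the Principal Investigator, who compiles that report, monitors safety under section 7.

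**Conclusion.** The concern holds in a conditional form. The recording rules in 7.2 and 7.3 are narrower than the definition in 7.1, section 9.2.3 does not name its source, and no one is named, or stated to be blinded, to judge relatedness. If the comparison is built from the investigator's record, and if attribution differs by arm, the result can be biased in either direction. If it is built from the caregiver log, this bias does not arise.

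The size cannot be derived from the documents. In the illustration, filtering out 10% of one arm's events hardly matters (5.4% to 6.5% rejection with no true difference), while filtering out half matters a great deal (25.5% to 48.1%). These figures rest on the assumed retention shares, on borrowed event rates, on one event per child and on all 170 children per arm being counted. The borrowed rates are for skin sensations, which may well be called related in both arms; for non-skin events, where attribution is more open, the documents give no rate.

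No sample-size figure changes. The point is worth correcting before the safety table is built, because the remedy is small.

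**What to change.** - **Sections 7.2 and 7.3:** state that every adverse event meeting the 7.1 definition is recorded for every child in both arms, with the caregiver log as a named source and relatedness as a separate field.
- **Section 9.2.3:** state that the between-group comparison uses all adverse events irrespective of relatedness, with related events shown second.
- **Relatedness:** state that existing study staff judge it from a form that omits the allocation. Preferably this is not an assessor still rating children at that site, since event details could give clues to the arm.
- **Appendix 5, A5.1:** clarify that the DSMC summaries cover all serious adverse events, whatever the relatedness call.

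The cost is wording in four places and one form field, with no new staff. The downside is a longer event listing and a little extra form work. Comparing all events removes the attribution bias from the main comparison; the masked judgement then protects the secondary, related-event table and the reporting decision.

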## 7.4 Complaint Handling

If there is any complaint of the tPCS, the Principal Investigator and Co-Investigators will be informed immediately to rectify the issue. If the subject is unable to tolerate the tPCS, the study will be discontinued for the subject.

## 8 Data Analysis

### 8.1 Data Quality Assurance

All study team members will be trained in the study-related procedures as delegated to ensure that collected data is reliable and complete. Identifiable patient data will be anonymized. Access to the data will only be open to the Principal Investigator and Co-Investigators. The Principal Investigator and Co-Investigators will ensure adherence with the protocol and accuracy in relation to data entry. Quality of the data will be ensured and monitored every month during the study period, the Principal Investigator and Co-Investigators will maintain essential study documents (protocol and amendments, source documentation, relevant correspondence, and all other supporting documentation) in a confidential manner as required by the approving ethics committee.

### 8.2 Data Entry and Storage

Data may be first recorded on hard copies of the standardized data forms of ATEC, ABC and CSHQ (*see Appendix 1-3 for data forms*), and subsequently keyed into a secure password-protected document on a shared drive among the eight sites. Data entry and subsequent data quality checks will be performed by two designated personnel at each site, at the end of every month during the study period. Access to the data will only be open to the study investigators. The Principal Investigator and Co-investigators will ensure accuracy of the data entered. Hardcopy of the data forms will be stored in locked cupboards in the respective hospital pediatric departments.

## 9 Sample Size and Statistical Methods

### 9.1 Determination of Sample Size

Based on a two-sided paired t-test at 80% power, 5% one-sided alpha and an expected effect size of small (0.20) when using bilateral frontal montage and medium (0.52) when using prefrontal-cerebellar montage, we will use an average of 0.36 effect size to compute the sample size, which leads to 120 per group. Based on an estimated 40% drop-out rate due to potential implications from post- COVID heightened travelling restrictions in Guangdong province, a sample size of 339 is required. We will use 340 as the sample size for recruitment in this study.

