tPCS delivers pulsed currents at a predetermined frequency to the cortex, as opposed to the direct current provided by tDCS. Studies involving tPCS have demonstrated effects on resting state functional connectivity, reported to facilitate interhemispheric coherence and enhance cortical plasticity. These neural impact of tPCS may be of relevance to ASD since widespread prefrontal-posterior underconnectivity and atypical information processing between brain regions are well-established in this disorder. Furthermore, children with ASD were found to have elevated global excitation-inhibition (E/I) ratio which could serve as a consistent neuromodulatory target in treating ASD across children with heterogenous etiology. EEG bands may act as proxy markers for neural excitation and inhibition and tPCS has been evidenced to increase/decrease EEG band power in a frequency-specific manner, indicating its potential therapeutic application in ASD via modulating highly associated brain regions such as the prefrontal cortex and the cerebellar to target E/I imbalances. In fact, a previous study using mouse models of ASD-linked genes demonstrated that modulating activities of cerebellar-prefrontal circuits improved social impairments and inflexible behaviours, purported to be due to the activation of GABAergic Purkinje cells in the cerebellar Rcrus1 and the posterior vermis.

Finally, in studies involving children with ASD and transcranial direct current stimulation (tDCS), the most common type of tES used in research, positive improvements in ASD evaluation scores have been reported after stimulation of the L-dLPFC, the cerebellar or both the L-dLPFC and the cerebellar. For example, in a study involving 16 ASD children, it was reported that 20 sessions of 20 min, 1 mA prefrontal-cerebellar tDCS stimulation resulted in a significant reduction in severity of ASD global symptoms as measured by the Aberrant Behaviour Checklist (ABC) and the Autism Treatment Evaluation Checklist (ATEC) in the active stimulation group compared to the sham stimulation group. In another small open label, the quality of sleep and mood in participants was reported to have improved, in addition to a 25% reduction in ABC scores.

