### **2.2 Primary Objective and Outcome measures**

The primary objective is to evaluate the effectiveness of tPCS in addition to standard therapy in improving social functioning in children with ASD, aged 3 to 14 years old. The primary outcome measure will be the change in mean scores as measured by the Autism Treatment Evaluation Checklist (ATEC), for both ATEC total and subdomain scores, at post-treatment compared to baseline. The secondary outcome measure will be the change in mean scores as measured by the Autism Behaviour Checklist (ABC), for both ABC total and subdomain scores, at post-treatment compared to baseline.

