### 9.2 Statistical and Analytical Plans

#### 9.2.1 General Considerations

Statistical analysis will be implemented using the IBM SPSS version 27.0. Before applying any statistical test, the data sets will be tested for a normal distribution with the Shapiro–Wilk test. If the data was found to be normally distributed, then one- way analysis of variance ANOVA and Student’s t-test will be used for the comparison between groups. Analysis of Covariance ANCOVA will be used to compare one or more means between groups

while controlling for the effects of one or more covariates (continuous variables that are related to the dependent variable). For comparison with the baseline value, paired t-test or one-way analysis of variance (ANOVA) will be used to compare the differences within the group before and after treatment. If the data was found to be not normally distributed then Kruskal-Wallis test or Mann-Whitney rank-sum test was used for the comparison. In order to correct for multiple comparisons, Bonferroni correction will be used to further validate the significance of each p-value. All statistical tests were conducted using a two-sided test. The  $\alpha$ -value was set to 0.05 for all the statistical tests and < 0.01 for Bonferroni correction. Chi-Squared test was used for categorical data, and Mann-Whitney rank sum test was used for ordinal data.

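### The 80% power in section 9.1 carries the wrong test label, rests on an effect size not justified for active versus sham on ATEC, and falls to 72.5% at the plan's own 40% drop-out

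*Combined protocol and SAP*

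**What the plan says.** Section 9.1 opens its calculation with "Based on a two-sided paired t-test at 80% power, 5% one-sided alpha". It takes 0.20 from reference 35 (bilateral frontal montage) and 0.52 from reference 67 (prefrontal-cerebellar montage), and continues: "we will use an average of 0.36 effect size to compute the sample size, which leads to 120 per group". It then allows for 40% drop-out, reaches 339 and rounds to 340. Section 4.2 puts 170 in each group.

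Other sections bear on this:

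- **Test used.** Section 9.2.1 states "All statistical tests were conducted using a two-sided test", with alpha 0.05. It uses the paired t-test for change within a group and the t-test, ANOVA or ANCOVA between groups.
- **Comparison.** Section 4 describes a parallel-group, sham-controlled trial. Section 2.2 says "The primary outcome measure will be the change in mean scores as measured by the Autism Treatment Evaluation Checklist (ATEC"), at post-treatment against baseline.
- **Source of the 0.52.** Section 1.2.2 describes reference 67 as a small open-label study. It reports better sleep and mood, "in addition to a 25% reduction in ABC scores". The sentence before expands ABC as the Aberrant Behaviour Checklist, whereas this trial's own ABC is the Autism Behaviour Checklist (sections 2.2 and 4.3). No ATEC result is given for reference 67.
- **Drop-out.** The Protocol Deviations section expects 30% to 40%. Section 3.8 foresees imputation for an intention-to-treat analysis.

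**The concern.** A reader of section 9.1 learns that the trial has 80% power, but cannot tell for which comparison or on what evidence. The named test is a within-group one, and its sidedness contradicts itself. The planning effect is a plain average of two values from different montages, and the section does not say on which scale, or for which contrast, either was obtained. One source is open label, and the sham arm exists precisely to remove what an open-label result can contain. The drop-out allowance also needs checking, because it decides whether the intended 120 per arm would remain.

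At stake is how the result is read. If the trial is described as having 80% power and finds no difference, readers will take that as stronger evidence against a modest benefit than the design can give.

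**Working it through.** **Inputs.** Effects 0.20 and 0.52, average (0.20 + 0.52)/2 = 0.36; power 80%; alpha 5%; 120 per group; 40% drop-out; 340 enrolled (all section 9.1). 1:1 allocation, 170 per group (section 4.2). Two-sided testing (section 9.2.1).

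**1. Reproducing 120 per group.** For two independent groups, two-sided:

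n per group = 2(z₀.₉₇₅ + z₀.₈₀)² / d² = 2(1.960 + 0.842)² / 0.36² = 121.1, so 122. The noncentral t gives 122.1.

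The four readings of the label at d = 0.36 and 80% power, by noncentral t:

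| Test | Needed |
|---|---|
| Two-sample, two-sided 5% | 122 per group |
| Two-sample, one-sided 5% | 96 per group |
| Paired, two-sided 5% | 63 pairs |
| Paired, one-sided 5% | 50 pairs |

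Only the first is close to 120. The calculation is a between-arm one, and the words paired and one-sided do not describe it.

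**2. Dependence on the averaged effect, at 120 per arm.** Two-sample, two-sided 5%, noncentrality d√(n/2), 2n − 2 degrees of freedom. At d = 0.36 the noncentrality is 0.36 × √60 = 2.79 and power is 79.3%.

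| d | Power at 120 per arm | Needed per arm for 80% (normal approximation) |
|---|---|---|
| 0.20 | 33.9% | 393 |
| 0.36 | 79.3% | 122 |
| 0.52 | 98.0% | 59 |

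The plan's two source values imply 34% or 98%. The 80% arises only at their midpoint.

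**3. Drop-out, a separate matter.** 340 × (1 − 0.40) = 204, or 102 per arm. The stated 339 matches multiplication, 242 × 1.4 = 338.8. Keeping 120 per arm after 40% loss would need 240/0.6 = 400.

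| Analysed per arm | d = 0.20 | d = 0.36 | d = 0.52 | Detectable d at 80% |
|---|---|---|---|---|
| 102 (40% lost) | 29.5% | 72.5% | 95.9% | 0.394 |
| 120 (as stated) | 33.9% | 79.3% | 98.0% | 0.363 |
| 170 (none lost) | 45.2% | 91.1% | 99.8% | 0.305 |

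At d = 0.36, the fall from 79.3% to 72.5% is due wholly to drop-out, not to the origin of the effect size.

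**The case against.** **Power is conditional on the assumed effect.** If the true between-arm difference is 0.36, then 120 per arm does give about 80%. This stands. A reader might infer from the paired label that the 80% belongs to a within-group contrast. Step 1 rules that out: a paired test would need 63 or 50 pairs. What is open to challenge is the support for 0.36.

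**The origin of the 0.52 is not documented.** A reader might infer that it was measured on a scale other than ATEC, or that it is an uncontrolled pre-post change. Both are plausible from section 1.2.2, but neither is stated. Open label means unblinded, not necessarily single-arm. Section 9.1 names no outcome or contrast, and section 1.2.2 does not say that ATEC was not measured. The gap is therefore missing justification, not a demonstrated mismatch. The same holds for the 0.20, which serves here as a sensitivity point and not as a better estimate.

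**There is closer evidence.** Section 1.2.2 also describes a sham-controlled prefrontal-cerebellar study in 16 children, with a significant reduction on ABC and ATEC against sham. It supports the direction of effect on this contrast and scale. The document gives no effect size for it, and section 9.1 does not use it.

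**102 per arm may be pessimistic.** At 30% drop-out, 119 per arm remain and power at 0.36 is 79.0%. With imputation, the number analysed could be higher. This stands, and is why the range up to 170 is shown. But 40% is the rate on which section 9.1 bases its total.

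**A one-sided test would suffice.** At one-sided 5%, 102 per arm gives 82% at 0.36. Section 9.2.1 excludes this by making all tests two-sided.

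**Conclusion.** The point holds in three parts.

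1. **Label.** Section 9.1 describes a test that does not produce its figure. The 120 per group comes from a two-sample, two-sided 5% comparison at d = 0.36, which is the comparison the trial makes.
2. **Effect size.** Nothing in the documents justifies 0.36 as an active-minus-sham difference in ATEC change. Power at 120 per arm runs from 34% to 98% across the two values averaged.
3. **Drop-out.** At the plan's own 40%, 102 per arm remain. Power at 0.36 is then 72.5%, and 80% power is reached only at 0.394.

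The documents do not show that the true effect is smaller than 0.36, nor that the trial is underpowered if most children are analysed: with all 170 per arm, power at 0.36 is 91%. The figures assume a standardised difference between equal arms, the unadjusted two-sided 5% level, and analysis of the stated number per arm. They take no credit for covariate adjustment and make no allowance for the stricter Bonferroni threshold in section 9.2.1.

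**What to change.** Reword section 9.1 as follows.

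- Replace the paired and one-sided wording with a two-sample, two-sided 5% comparison of ATEC change between arms.
- State that 340 enrolled gives 80% power for a standardised difference of 0.394 if 40% drop out (102 per arm), and of 0.305 if all 170 per arm are analysed.
- Give power at 0.20 and 0.36: 29.5% and 72.5% with 102 per arm; 45% and 91% with 170 per arm.
- State that 0.36 is an assumed value, drawn partly from an open-label study, and not an estimate of the sham-controlled ATEC effect. Where the team has the sources, add the scale and contrast behind 0.20 and 0.52.

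This is a change of wording only and needs no extra patients. Its cost is that the stated power at the plan's own drop-out rate falls from 80% to about 73%.

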## Protocol Deviations

There were two protocol deviations. The Study Protocol deviation was directly associated with the coronavirus disease 2019 (COVID-19) pandemic. During the early part of the trial in 2022, China held on to extremely stringent post-COVID travelling restrictions, as many citizens were still not vaccinated and the country held on to a “zero-infection” policy. This had a tremendous negative impact on the recruitment process of this trial.

Given the circumstances, the Principal Investigator and the study team members estimated the potential drop-out rate may increase to 30% - 40%. After discussing with IRB, we decided to 1) increase the sample size by 40%, from 240 subjects to 340 subjects to account for potential dropouts, and 2) expanded from seven to eight recruiting hospital sites with the addition of Shenzhen Luogang Maternal and Child Health Hospital, in order to facilitate the recruitment of an enlarged sample size. Both protocol deviations were included in this Trial Protocol Version 1.1.

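### The 40% dropout allowance multiplies by 1.4 instead of dividing by 0.6, so 340 children leave about 102 per group and 72% power, not 120 per group and 80%

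*Combined protocol and SAP*

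**What the plan says.** All of the sizing is in section 9.1 of the combined protocol and SAP.

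- **Test, power and alpha:** "Based on a two-sided paired t-test at 80% power, 5% one-sided alpha".
- **Effect size and evaluable number:** 0.20 from one cited study and 0.52 from another are averaged, and "we will use an average of 0.36 effect size to compute the sample size, which leads to 120 per group".
- **Dropout:** "Based on an estimated 40% drop-out rate", attributed to travel restrictions.
- **Result:** "Guangdong province, a sample size of 339 is required. We will use 340 as the sample size for recruitment in this study".

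The Protocol Deviations section, near the front of the document, puts anticipated dropout at 30% to 40% and describes the enlargement as a decision to "increase the sample size by 40%, from 240 subjects to 340 subjects to account for potential dropouts". Section 3.8 says that dropouts are not replaced. Section 4.2 puts 170 children in each group.

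On the analysis side, section 9.2.1 says "All statistical tests were conducted using a two-sided test", and that the alpha "value was set to 0.05 for all the statistical tests".

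**The concern.** There are three faults in one short paragraph, and the first carries the consequence.

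1. **Inflation.** Adding 40% to a sample does not allow for losing 40% of it. If a fraction *d* is lost, the number to enrol is n/(1 − *d*), not n × (1 + *d*). At *d* = 0.40 the two differ by a factor of 1/(0.60 × 1.40) = 1.19.
2. **Test.** The trial compares two randomised parallel groups. A paired t-test compares before with after within one group, which is not the comparison in the section 2.1 hypothesis.
3. **Sidedness.** The sizing sentence says two-sided and then "5% one-sided alpha". Section 9.2.1 allows two-sided tests only.

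This paragraph is the only justification for the enrolment figure; section 3.1 refers to it. If its 80% does not follow from its own assumptions, a null result will be read against more power than the design provides at the planned dropout. A reader also cannot tell which test and which alpha the number belongs to.

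**Working it through.** **Inputs.** Effect size 0.36 = (0.20 + 0.52)/2, power 80%, 120 per group, 40% dropout, 339 rounded to 340 (section 9.1). Dropout range 30% to 40% (Protocol Deviations). Two-sided 0.05 (section 9.2.1). Equal allocation, 170 per group (section 4.2). No replacement (section 3.8).

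**Step 1. Which calculation gives 120?** For two independent groups, n per group = 2(z₁₋α + z₁₋β)²/d² with the normal approximation, taking α/2 for a two-sided test. The t-based figures use the noncentral t distribution.

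| Test at d = 0.36, 80% power | Normal | t-based |
|---|---|---|
| Two-sample, two-sided 5% | 2(1.960 + 0.842)²/0.36² = 121.1 per group | 122.1, so 123 per group |
| Two-sample, one-sided 5% | 95.4 per group | 96.1, so 97 per group |
| Paired, two-sided 5% | – | 62.5, so 63 pairs |
| Paired, one-sided 5% | – | 49.1, so 50 pairs |

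Only the first row comes near 120. It also agrees with section 9.2.1. At exactly 120 per group its t-based power is 79.3%.

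**Step 2. Which inflation gives 339?**

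- Multiplying: 121.1 × 2 × 1.4 = 339.1. From the rounded total, 240 × 1.4 = 336.
- Dividing: 240/0.60 = 400. From the unrounded figure, 121.1 × 2/0.60 = 403.7.
- Dividing at 30% dropout: 240/0.70 = 342.9. This is close to 340, but it is not the 40% that section 9.1 states.

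The intermediate 121.1 is not printed in the plan, so the route is inferred. It matches 339, and the Protocol Deviations text describes the same step as a 40% increase.

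**Step 3. What does 340 deliver at 40% dropout?**

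- Completers: 340 × 0.60 = 204, that is 102 per group.
- Noncentrality: 0.36 × √(102/2) = 2.571.
- Power, two-sided 5%: about Φ(2.571 − 1.960) = 72.9% with the normal approximation, and 72.5% with the noncentral t. Type II error is 27.5% rather than 20%.
- Effect detectable with 80% power at 102 per group: 0.39.

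**Step 4. How much dropout does 340 tolerate?**

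- To keep 240: 1 − 240/340 = 29.4%.
- To keep 246 (123 per group): 1 − 246/340 = 27.6%.
- At 30% dropout, 340 × 0.70 = 238, that is 119 per group, with 79.0% power.

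**Step 5. Sensitivity at 102 per group.**

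- Two-sided 5%, at the two effect sizes that were averaged: 30% power at 0.20 and 96% at 0.52.
- One-sided 5%, at 0.36: 82% power.

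**The case against.** The strongest reply is that 40% is the top of the plan's own range. At 30% dropout the trial keeps 119 per group and 79.0% power, against 79.3% at the stated 120, so 340 is practically enough there. That is correct, and it limits how far the finding reaches: the shortfall is conditional on dropout, and the documents do not give the realised rate. It does not rescue the calculation, because section 9.1 sizes on 40% and claims 339 for that rate.

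Second, a dropout is not always a lost outcome. Section 3.7 also counts children with interrupted treatment or poor compliance, and section 3.8 plans best-effort assessment and imputation for an intention-to-treat analysis. So 102 per group is a completers-only figure. This stands as a caveat. Section 9.1 takes no credit for recovered data, and children kept in the analysis without full treatment may dilute the effect.

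Third, section 9.2.1 lists ANCOVA, which could regain power. As an illustration, assume 0.36 is a change-score effect and the baseline score is the covariate. The effective size is then 0.36 × √(2/(1 + ρ)), and power at 102 per group is about 79% for a baseline correlation ρ of 0.7 and 89% for 0.3. The plan names neither the covariates nor the correlation, so this cannot support the stated number. It does show that 72% belongs to an unadjusted comparison.

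Fourth, a one-sided 5% test gives 82% at 102 per group. Section 9.2.1 excludes it, and one-sided sizing would have given 97 per group, not 120.

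Fifth, section 9.2.1 also mentions a 0.01 level for Bonferroni correction. At that level, power for 0.36 is 59% with 123 per group and 49% with 102. This does not weaken the finding, but a restated power figure must say which alpha and how many endpoints it covers.

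**Conclusion.** The concern holds. At the plan's own 40% dropout, 340 children give 102 per group and 72.5% power at an effect size of 0.36, not 120 per group and 80%. Keeping 120 per group would take 400. The shortfall is about 7 percentage points of power, and it shrinks to almost nothing if dropout is near 30%. It does not bias the treatment estimate or affect type I error.

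The words *paired* and *one-sided* are also wrong as written: none of the calculations they imply gives 120 per group.

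The power figure assumes an independent two-sample t-test at two-sided 5% on one endpoint, with dropouts contributing no outcome data. This is the only reading that comes near the plan's 120 and agrees with section 9.2.1. The correction is needed because the paragraph is the sole basis for the enrolment number.

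**What to change.** Replace the calculation in section 9.1 with text to this effect:

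> Independent two-sample t-test, two-sided alpha 0.05, 80% power, standardised between-group difference 0.36: 123 evaluable children per group (246 in total). With 340 randomised, this is held up to 28% dropout. At 40% dropout (102 per group), power is 72%. These figures apply to one endpoint without adjustment for multiplicity.

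Remove the references to a paired test and to a one-sided alpha. The last sentence of the proposed text keeps the power statement from being read as covering the Bonferroni level in section 9.2.1.

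In the Protocol Deviations section, leave the record of what was decided and add a note that the 40% increase offsets about 29% dropout (1 − 240/340), not 40%.

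The cost is a few sentences of protocol wording and a less favourable power statement at 40% dropout. No extra enrolment is asked for.
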